## Abstract

**Introduction:**

Automated systems for ventilator management to date have been either fully heuristic rule-based systems or based on a combination of simple physiological models and rules. These have been shown to reduce the duration of mechanical ventilation in simple to wean patients. At present, there are no published studies that evaluate the effect of systems that use detailed physiological descriptions of the individual patient.

The BEACON Caresystem is a model-based decision support system that uses mathematical models of patients’ physiology in combination with models of clinical preferences to provide advice on appropriate ventilator settings. An individual physiological description may be particularly advantageous in selecting the appropriate therapy for a complex, heterogeneous, intensive care unit (ICU) patient population.

**Methods and analysis:**

Intenive Care weaning (iCareWean) is a single-blinded, multicentre, prospective randomised control trial evaluating management of mechanical ventilation as directed by the BEACON Caresystem compared with that of current care, in the general intensive care setting. The trial will enrol 274 participants across multiple London National Health Service ICUs. The trial will use a primary outcome of duration of mechanical ventilation until successful extubation.

**Ethics and dissemination:**

Safety oversight will be under the direction of an independent committee of the study sponsor. Study approval was obtained from the regional ethics committee of the Health Research Authority (HRA), (Research Ethic Committee (REC) reference: 17/LO/0887. Integrated Research Application System (IRAS) reference: 226610. Results will be disseminated through international critical care conference/symposium and publication in peer-reviewed journal.

**Trial registration number:**

ClinicalTrials.gov under NCT03249623. This research is registered with the National Institute for Health Research under CPMS ID: 34831.

Strengths and limitations of this studySingle-blinded multicentre randomised control trial evaluating management of mechanical ventilation as directed by the BEACON Caresystem compared with that of standard care in the general intensive care setting.The BEACON Caresystem is a model-based decision support system that uses mathematical models of patients’ physiology in combination with models of clinical preferences to provide advice on appropriate ventilator settings.Sample size was determined by a power analysis of the duration of mechanical ventilation.Patients and the public were not involved in the design of this study.The study does not assess successful rehabilitation of the patient subsequent to their intensive care unit stay.

## Introduction

Optimising mechanical ventilator management has been the focus of much research, seeking to decrease ventilator-associated complications such as ventilator-associated lung injury, ventilator-associated pneumonia, respiratory muscle atrophy and patient discomfort.^1 2^ Increased duration of mechanical ventilation and prolonged weaning increases the number of these complications with a vicious cycle that leads to increased morbidity and mortality and associated economic costs.^2^ Protocols and computerised tools aiming to reduce length of mechanical ventilation might therefore be beneficial.

Weaning protocols and nurse-lead ventilator management is routinely used in the intensive care setting.^2 3^ Such approaches have been shown to reduce the duration of mechanical ventilation.^3^ However, standardising this process is important, and the quality and quantity of nursing care are a critical factor in reducing duration of mechanical ventilation.^4^

Standardisation of care through automation or bedside decision support continues to be driven by novel technological innovation, some of which is already established in clinical practice.^3 5^ However, to date, much of this has been predicated on clinical guidelines rather than using detailed physiological descriptions of the individual patient.^6–8^ A Cochrane review of weaning trials with current systems concluded that their use may reduce duration of weaning, but highlighted that the population was predominantly composed of those who are ‘simple to wean’.^5^ The patient populations of these studies were characterised as without additional lung pathology and were predominantly ventilated for periods of less than 48 hours.^5^ Consequently, it remains to be investigated whether decision support systems can reduce duration of mechanical ventilation in patients with more than a few hours of ‘routine’ postoperative intubation. The BEACON Caresystem is a model-based decision support system that uses mathematical models of patients’ physiology in combination with models of clinical preferences to provide advice on appropriate ventilator settings.^9^ An individual physiological description may be particularly advantageous in selecting the appropriate therapy for a complex, heterogeneous, intensive care unit (ICU) patient population. The BEACON Caresystem is the commercial version of the INVENT system, which has been retrospectively evaluated in postoperative cardiac patients and patients with severe lung disease, and prospectively evaluated in providing advice on correct levels of inspired oxygen.^10–13^ To date, the commercial system has been evaluated over short durations of time from 4 to 8 hours to establish whether physiological measurements are improved.^14 15^ No previous studies evaluating outcome of weaning from mechanical ventilation have been performed.

Here, we describe a single-blinded multicentre randomised control trial evaluating management of mechanical ventilation as directed by the BEACON Caresystem compared with that of current care in the general intensive care setting.

## Methods and analysis

### Administrative structure

The study is under the auspices of the eHRA, REC reference: 17/LO/0887, IRAS reference: 226610, and with the National Institute for Health Research under CPMS ID: 34 831. The research and development department of the Chelsea and Westminster National Health Service (NHS) Foundation Trust is sponsor of the study and responsible for study conduct, safety monitoring, personnel training and randomisation. Data collection occurs at participating centres, with data analysis performed in collaboration with the respiratory and critical care group, Aalborg University and independent statisticians of the study sponsor. All data transfer and storage will be performed in accordance with General Data Protection Regulation (GDPR) regulations and the study will monitor and review interim analysis and made recommendations to the steering committee.

### Study design

To test the hypothesis that following advice from the BEACON Caresystem will reduce time to successful extubation, the Intenive Care weaning (iCareWean) group has designed a single-blinded multicentre randomised control trial evaluating management of mechanical ventilation as directed by the BEACON Caresystem compared with that of current care in the general intensive care setting. The Consolidated Standards of Reporting Trials (CONSORT) flow diagram of the study is illustrated in figure 1.

**Figure 1 F1:**
[figure not shown]
Consolidated Standards of Reporting Trials flow diagram for protocol. MV, mechanical ventilation.

### Description of the BEACON Caresystem

At the core, functionality of the BEACON Caresystem is a set of physiological models including models of pulmonary gas exchange, acid–base chemistry, lung mechanics and respiratory drive.^9^ The BEACON Caresystem tunes these models to the individual patient so that they accurately describe the current physiological measurements. Once the models are tuned, they are then used by the system to simulate the effects of a change in ventilator settings. The results of these simulations are then used to calculate the clinical benefit of changing the ventilator settings by balancing the competing goals of mechanical ventilation using mathematical models of clinical preference.^9 10^ Appropriate ventilator settings imply a balance between quantified preferences of several competing clinical goals. For oxygenation, the preferred values of inspired oxygen fraction are weighed against the need to prevent hypoxaemia. For settings of ventilation volume, pressures or frequency, the risk of lung trauma is weighed against the need to prevent acidosis. For settings of support in spontaneously breathing patients, the risk of respiratory muscle atrophy on over support is weighed against the excessive work of breathing and potential of respiratory muscle fatigue on under support. Quantification of these risks is used to calculate a total score for any possible ventilator strategy. The system then calculates advice so as to change ventilator settings to improve this score.

The BEACON Caresystem functions as an ‘open-loop’ system. This means that the advice provided by the system is presented to the clinician. The ventilator settings are then changed by the clinician, and the patient’s response to these changes is automatically registered and used by the BEACON Caresystem to retune the physiological models and repeat the process of generating new advice.

The BEACON Caresystem provides advice on ventilator settings including the following. Values for maximal advice steps are given in table 1.

Fraction of inspired oxygen (FiO_2_).Tidal volume (Vt).Respiratory frequency (f).Positive end expiratory pressure (PEEP).Pressure above PEEP.

**Table 1 T1:** Maximal steps in mechanical ventilation advice provided by BEACON Caresystem

Maximal allowed step in ventilator settings	Stepping up	Stepping down
FIO_2_	10 %	5% or 2% when SpO_2_ ≤92 %
Vt (volume modes)	50 mL	50 mL
Respiratory frequency (f)	5 breaths/min or 3 breaths/min when f≥18	5 breaths/min
Pressure above PEEP (pressure modes)	2 cm H_2_O	2 cm H_2_O
PEEP	3 cm H_2_O if PEEP <10 cm H_2_O, otherwise 2 cm H_2_O	2 cm H_2_O

f, respiratory frequency; FiO2, fraction of inspired oxygen; PEEP, positive end expiratory pressure; Vt, tidal volume.

### Patient screening

All patients will be screened for eligibility on admission to the ICU by the research team, including research nurses and clinical research fellows. Advice will be obtained from relatives acting as a personal consultee, or consultant acting as nominated professional consultee. Retrospective consent is then obtained from the patient on regaining capacity. The study will run from September 2017 to November 2020.

### Eligibility criteria

#### Inclusion criteria

At least 24 hours of invasive mechanical ventilation.Age ≥18 years.Patient is mechanically ventilated in a ventilator mode, and by a ventilator, supported by the BEACON Caresystem.Haemodynamically stable, where instability is defined by the presence of two or more of the following criteria: acidosis pH <7.2, poor urine output <0.5 mL/kg/h, use of vasopressors, for example, noradrenaline >25 µg/min.

#### Exclusion criteria

The absence of an arterial catheter for blood sampling.Medical history of home mechanical ventilation which may lead to prolonged stay in the ICU, including long-term oxygen therapy and non-invasive ventilation not associated with sleep apnoea.Clinical conditions requiring treatment with extracorporeal membrane oxygenation (ECMO), that is, an inspired oxygen of 100% for more than 24 hours.Head trauma or other conditions where intracranial pressure may be elevated and tight regulation of arterial CO_2_ level is paramount.Primary (non-overdose related) neurological patients (Glasgow Coma Score 24).Severe heart failure classified by grade 4 American Heart Association guidelines.End-stage liver disease.Multiple ICU admissions within the medical stratification group, that is, more than one admission.Corrective orthognathic surgery.ICU admission following oesophageal surgery.Patients with morbid obesity defined as either body mass index (BMI)≥45; or BMI≥35 with an Acute Physiology and Chronic Health Evaluation II (APACHEII) score on admission >24.Pregnancy.Mechanical ventilation initiated for more than 24 hours in other centres.

### Randomisation

Figure 1 illustrates the CONSORT flow diagram for the study. On recruitment to the trial, participants are randomised to either to the intervention group where advice is provided by the BEACON Caresystem, or to the control arm where standard care is provided. Block randomisation is applied with each block stratified to ensure equal distribution between control and intervention arm for the following patient groups, reducing the risk of potential bias by over-representation of these groups in the control or intervention arms:

Surgical or medical ICU admission.Presence of absence of chronic obstructive pulmonary disease.Primary thoracic or non-thoracic medical diagnosis.

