Duration of mechanical ventilation to successful extubation following randomisation defined as the time from randomisation and until successful extubation, with successful extubation defined as ≥48 hours of unassisted spontaneous breathing after extubation.Time from control mode to support mode defined as the time following randomisation, from initiation of control modes of ventilation and until initiation of support modes of ventilation.Time from support mode to successful extubation defined as the time following randomisation, from initiation of support modes of ventilation and until successful extubation.Number of changes in ventilator settings per day defined as the daily registered number of changes to ventilator settings from randomisation until successful extubation.Time to first SBT defined as the time from randomisation to the first performed SBT.Time to first successful SBT defined as the time from randomisation to the first successful SBT.Time to first extubation defined as the time from randomisation to the first extubation attempt.Time to first disconnection from mechanical ventilation defined as the time from randomisation to the point at which mechanical ventilation is first discontinued.Percentage of time in control mode ventilation defined as the time from randomisation which is spent in controlled modes of mechanical ventilation in per cent of duration of mechanical ventilation.Percentage of time in support mode ventilation defined as the time from randomisation which is spent in support modes of mechanical ventilation in per cent of duration of mechanical ventilation.Use of sedatives defined as the cumulative use of sedative drugs from randomisation until successful extubation.Use of neuromuscular blockading agents defined as the cumulative use of neuromuscular blockading agents from randomisation until successful extubation.Number of intubation free days defined as the number of days without intubation from randomisation until successful extubation.Number of reintubations defined as the number of reintubations following extubation from randomisation until successful extubation.Number of tracheostomies defined as the number of patients having tracheostomy performed from randomisation until successful extubation or protocol end.Number of patients on prolonged mechanical ventilation defined as the number of patients on mechanical ventilation ongoing for more than 21 days after the start of mechanical ventilation.Number and types of adverse events related to mechanical ventilation defined as the incidence of adverse events directly related to mechanical ventilation.ICU mortality defined as the mortality from randomisation and until death or ICU discharge.Length of stay defined as the duration of ICU admission from the start of mechanical ventilation and until death or ICU discharge.Mobilisation times defined as the time from randomisation until (1) first mobilisation, for example, sitting on the edge of the bed, standing up and marching on the spot and (2) regaining independency, for example, able to drink/eat or comb hair.Daily patient physiological blood gas status defined as daily ABG values of SaO_2_, PaO_2_, PaCO_2_, pH from randomisation until successful extubation.Daily average physiological status defined as daily averages of measured values of oxygenation (SpO_2_), end-tidal CO_2_ fraction (EtCO_2_), ventilation (respiratory rate, tidal volume, anatomical dead space), pulmonary mechanics (airway pressure, respiratory system compliance) and ventilator settings as measured routinely at the bedside.

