
### Statistical considerations

Sample size was determined by a power analysis of duration of mechanical ventilation. Extrapolation of the 2016 ICU admission data from two London-based NHS hospitals provided a sample size of 548 patients over an 18-month period. In these patients, mean total duration of mechanical ventilation measured in days was 7.2, with an SD of 7.0 days. A study population of 137 patients in each randomisation group would allow detection of a 2 day or 30% improvement in the duration of mechanical ventilation in the BEACON Caresystem group assuming a similar improvement in SD, with an α level of 0.05 and power of 0.8. A 2 days or 30% reduction in duration of mechanical ventilation is similar to that used previously.^6^

Primary and secondary outcomes will be measured across the protocol duration and comparison made by independent samples t-test, or appropriate non-parametric testing if not normally distributed. Complementary analysis will be performed using Kaplan-Meier curves.

The study is not sufficiently powered to allow subgroup analysis for the groups specified in the randomisation strategy.

An independent data safety monitoring committee will be established as part of the study, with this committee responsible for defining stopping criteria. Safety data will be looked at after the first 80 patients have been recruited, with an interim analysis performed following 50% recruitment.

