The results of this study compare care provided with the system’s advice with current clinical practice at study sites. As there is no standard of care or usual method of weaning in the UK, this study does not compare the system’s advice with that of best practice defined by clinical guidelines. To avoid comparing two interventional changes, no attempt will be made to standardise care in the control arm according to best practice.

As patients are studied for many days, it is not possible to store continuous waveform data for all patients at all times. Systematic analysis of patient-ventilator asynchrony will not therefore be possible.

This study excluded patients if ventilated for <24 hours. In doing so, patients ventilated post surgery defined previously as simple to wean are not included. This should not imply that the patients studied here are necessarily difficult to wean, but rather that they represent a broad cross section of mechanically ventilated patients not simply recovering from the effects of anaesthesia.

In addition, it is important to note that substantial training has been provided to all sites in the use of the BEACON Caresystem and the same clinical team treat patients for both the control and intervention arm. It is possible then that both training and use of the system influence routine care, potentially biasing study results.

This paper describes the study protocol of a randomised control trial evaluating the advice of the BEACON Caresystem in a general medical ICU population. This protocol represents an important step evaluating the use of advice over the whole of the ICU stay, and only in patients intubated greater than 24 hours. The results will indicate whether the BEACON Caresystem is a useful tool in optimising ventilation strategy.

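### Randomisation is stratified on three factors that the named test then ignores: if they are prognostic, the intervals are modestly too wide and a free gain in power is lost

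*Protocol article*

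**What the plan says.** In the protocol article, the Randomisation section describes block randomisation with "each block stratified to ensure equal distribution between control and intervention arm for the following patient groups". Three binary factors follow: surgical or medical admission, presence or absence of COPD, and a primary thoracic or non-thoracic diagnosis. Together they form eight cells. The stated purpose is to avoid bias from one arm holding too many patients of one kind. Site is not listed as a factor, although the abstract says: "The trial will enrol 274 participants across multiple London National Health Service ICUs".

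Statistical considerations covers primary and secondary outcomes in one sentence, with "comparison made by independent samples t-test, or appropriate non-parametric testing if not normally distributed". Kaplan-Meier curves are the only complement. No adjusted model or stratified test is named. The one remark there about the randomisation groups is that the trial lacks power for subgroup analysis within them.

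The sample size rests on historical data in which the "mean total duration of mechanical ventilation measured in days was 7.2, with an SD of 7.0 days". The article states: "A study population of 137 patients in each randomisation group would allow detection of a 2 day or 30% improvement", "assuming a similar improvement in SD, with an α level of 0.05 and power of 0.8".

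**The concern.** Stratified allocation keeps the arms nearly equal on the three factors. Variation between strata therefore largely cancels out of the treatment difference, which becomes more precise than under simple randomisation. An independent-samples t-test does not use this. Its standard error is built from the whole within-arm variance, including the part due to the strata.

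If the factors are related to ventilation time, the reported standard error is larger than the true one. The interval is then too wide, the test rejects less often than its nominal 5% under the null, and some of the power gained by stratifying is not used. This comes from the test that the article itself names, so it does not depend on a detail that an article may leave to a fuller document.

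**Working it through.** **Inputs.** From Statistical considerations: 137 patients per arm, a difference of 2 days, a control SD of 7.0 days, and an SD that improves in similar proportion (30% off 7.0 gives 4.9). α is 0.05, and two-sided testing is assumed because sidedness is not stated. The share of within-arm variance explained by the three factors, R², is not in the document. I use 0, 5%, 10% and 20%.

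**The plan's own figure.** With the average SD, (7.0 + 4.9)/2 = 5.95, n per arm = (1.96 + 0.84)² × 2 × 5.95² / 2² ≈ 139, and power at 137 per arm is 0.794. With separate variances, 49 + 24.01 = 73.01, n per arm is 143.3 and power at 137 is 0.782. The stated 137 is therefore close to reproduced, with power of 0.78 to 0.79. The rest uses separate variances.

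**Formulas.**
- Reported (unadjusted) SE = √(73.01/137) = 0.730 days, so the 95% half-width is 1.96 × 0.730 = 1.431 days.
- True SE under stratified allocation, which is also the adjusted SE = 0.730 × √(1 − R²).
- Excess width of the unadjusted interval = 1/√(1 − R²) − 1.
- True type I error of the unadjusted test = 2[1 − Φ(1.96/√(1 − R²))].
- Power, unadjusted = Φ((2 − 1.431)/true SE).
- Power, adjusted = Φ(2/true SE − 1.96).

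**Example at R² = 10%.** True SE = 0.730 × 0.949 = 0.693. Type I error = 2[1 − Φ(2.066)] = 0.039. Unadjusted power = Φ(0.569/0.693) = 0.794. Adjusted power = Φ(2/0.693 − 1.96) = 0.823.

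| R² (assumed) | True SE | Adjusted half-width | Unadjusted interval too wide by | Type I error, unadjusted | Power, unadjusted | Power, adjusted |
|---|---|---|---|---|---|---|
| 0 | 0.730 | 1.43 | 0% | 5.0% | 0.782 | 0.782 |
| 5% | 0.712 | 1.40 | 2.6% | 4.4% | 0.788 | 0.803 |
| 10% | 0.693 | 1.36 | 5.4% | 3.9% | 0.794 | 0.823 |
| 20% | 0.653 | 1.28 | 11.8% | 2.8% | 0.808 | 0.865 |

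**Simulation check.** The simulation had 274 patients, eight strata, blocks of 4 (assumed), a skewed outcome and 4,000 runs per setting. It compared a Welch t-test with a linear model containing the three factors and robust standard errors.
- R² 10%: type I error 0.041 unadjusted and 0.050 adjusted; power 0.814 and 0.841.
- R² 20%: type I error 0.031 and 0.054; power 0.805 and 0.864.
- R² 5%: type I error 0.050 and 0.057; power 0.797 and 0.814. The simulation error of a 5% rate is √(0.05 × 0.95/4,000) ≈ 0.003, so a departure as small as 4.4% against 5% is hard to see at this R².

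**Site.** With four sites (assumed) explaining 10% of variance, not stratified on, and strata that explain nothing, type I error was 0.055 unadjusted and 0.052 adjusted for site. Power was 0.780 and 0.826. With strata and site explaining 10% each, power was 0.794 unadjusted and 0.863 adjusted for both.

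**The case against.** The strongest reply is that the effect is small, harmless in direction and dependent on a number nobody has. Most of this stands. The document never says how strongly the factors predict ventilation time; it gives protection against bias from imbalance as the reason for balancing. At R² = 0 there is no loss. The error does not raise the false-positive rate or bias the estimate. The type I figures are for the t-test; with an SD of 7.0 against a mean of 7.2 for a quantity that cannot be negative, the non-parametric branch is likely, and it was not evaluated. What remains is that the named test does not match the allocation scheme, and that matching it costs nothing.

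A reader might infer more, in four ways that the document does not support.

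- **That the trial falls short of its planned power because of this.** It does not. Stratification slightly raises the unadjusted power, from 0.782 to 0.788–0.808 over the assumed range. Measuring the benefit of adjustment from 0.782 would overstate it, because that baseline ignores the stratification.
- **That leaving out site also makes the error bars wrong.** Site is not a listed stratifier, so the unadjusted standard error already covers chance imbalance between sites. Omitting site costs precision only.
- **That sites differ strongly because "there is no standard of care or usual method of weaning in the UK".** That remark in the Discussion explains what the control arm represents. The article gives no between-site figure.
- **That daily outcomes will be tested with patient-days treated as independent.** One is "Number of changes in ventilator settings per day defined as the daily registered number of changes to ventilator settings". Nothing in the article says that days are pooled, and one summary per patient makes the named test valid. How daily data are summarised can properly be left to a fuller document.

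**Conclusion.** The point holds as a modest efficiency and calibration issue confined to the three stratification factors. For an assumed R² of 5% to 20%, the unadjusted interval is about 3% to 12% too wide, the t-test's true type I error is 4.4% down to 2.8%, and adjustment gains about 1.5 to 6 points of power. These figures rest on the assumed R², two-sided testing at 0.05, 137 per arm, a 2-day effect, SDs of 7.0 and 4.9 days, and a normal approximation that the simulation broadly supports. The conclusions of the trial would not be invalid without the change. It is still worth making, because power at 137 per arm reproduces at 0.78 to 0.79, slightly under the stated 0.80, and adjustment recovers that margin if the factors explain about 5% of the variance or more.

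**What to change.** State in Statistical considerations that the primary comparison will be made with a model containing treatment and the three stratification factors. If duration is skewed, use a rank or log-rank test stratified by the same factors. Apply the same rule to the secondary outcomes that are compared between arms. Entering the factors as three main effects avoids relying on sparse cells among the eight combinations.

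Site may be added as a further term, described as an optional gain in precision and not as a correction of the standard error.

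The cost is a change of wording. The three factors are needed to randomise each patient, so no new data or patients are required. The change should be fixed before anyone sees outcome data by arm.
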